### Power and sample size

#### Teamwork climate

Prior research using similar interventions has shown that teamwork climate increases for all professionals, but the improvement is greatest for nurses [36, 39, 40]. Therefore, we estimated a target sample size of nurses using results from prior studies. A sample size of 68 achieves 90% power to detect a mean of paired differences of 4.0 with an estimated standard deviation of differences of 10.0 and with a significance level of 0.05 using a two-sided paired t-test [46]. This sample size reflects completed paired surveys for 17 nurses at each site and is extremely feasible based on prior studies [36, 39, 40].

#### Adverse events

We used data from the AHRQ National Scorecard on Rates of Hospital Acquired Conditions 2010 to 2015, which also uses the MPSMS methodology, to estimate current rates for the adverse events included in our study [47]. The national rate for adverse events included in our study is 89.3 per 1000 discharges. Based on prior studies, we conservatively expect a 33% reduction in the rate of adverse events as a result of our interventions [36, 48]. Importantly, adverse events have recently declined by approximately 4% each year [47]. Accounting for this trend, we estimate a need to enroll a target sample size of 1936 patients each year (482 per site per year) to have 90% power to detect a significant improvement in adverse events using a Poisson regression accounting for clustering of hospitals (r = 0.3).

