### Study sites

In collaboration with the Society of Hospital Medicine (SHM) and the American Nurses Association (ANA), we issued a national call for applications for the RESET project. We received 14 applications from hospitals throughout the U.S, each of which was independently assessed by two members of research team for need (i.e., similar interventions had not already been implemented), commitment, and potential for success. Four hospital sites were selected, with two hospitals in the Southeast U.S., one in the Midwest, and one in the West. All hospitals are nonprofit and have between 200 and 350 beds. Two are non-teaching hospitals and two are teaching hospitals, though neither is a major affiliate of a medical school.

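### The adverse-event sample size gives two totals (1936 and 4 × 482 = 1928), and its claim that 90% power allows for hospital clustering with r = 0.3 cannot be verified

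*Protocol article*

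**What the plan says.** All the figures come from the protocol article, Power and sample size, Adverse events, unless noted.

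- Baseline: "The national rate for adverse events included in our study is 89.3 per 1000 discharges".
- Effect: "we conservatively expect a 33% reduction in the rate of adverse events".
- Trend: "adverse events have recently declined by approximately 4% each year". The size is said to allow for this, but not how.
- Size: "a target sample size of 1936 patients each year (482 per site per year"), chosen "to have 90% power to detect a significant improvement in adverse events".
- Method: "using a Poisson regression accounting for clustering of hospitals (r = 0.3").
- Number of hospitals (Study sites): "Four hospital sites were selected".

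The paragraph does not say what kind of quantity r is, and it gives no alpha or sidedness for this outcome. The section on exploration and preparation says that each site chooses one Phase I unit and one or two Phase II units. The statistical analysis section for adverse events plans a difference-in-differences interaction of unit type and year, with standard errors robust to clustering by hospital.

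**The concern.** The sentence that fixes the size contains two totals that differ, and the smaller one is the per-site target that the research nurses would work to.

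The sentence also tells the reader that the 90% is already net of hospital clustering. In a phrase about clustering of hospitals, r is most naturally read as a within-hospital correlation. A value of 0.3 with several hundred patients per hospital would inflate the size enormously, yet 1936 is close to what a plain two-period Poisson comparison needs with no inflation. If no usable allowance was made, or if the calculation was for a simpler contrast than the planned one, a null interaction could be read as evidence of no effect from a study believed to have 90% power.

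**Working it through.** **1. Site arithmetic.** 4 × 482 = 1928, and 1936 / 4 = 484. The difference is 8 patients a year, and 8 / 1936 = 0.4%. Rounding does not turn 484 into 482.

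**2. Reproducing 1936 without clustering.** Assume alpha 0.05 two-sided, as in the teamwork climate calculation. For two periods compared by a Wald test on the log rate ratio:

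n per period = (1.960 + 1.282)² × (1/λ0 + 1/λ1) / (ln RR)², with RR = 0.67, (ln 0.67)² = 0.1604 and (1.960 + 1.282)² = 10.507.

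| Trend applied to baseline | λ0 | λ1 = 0.67 λ0 | n per period | Power at 1936 | Power at 1928 |
|---|---|---|---|---|---|
| none | 0.0893 | 0.0598 | 1829 | 91.5% | 91.4% |
| one year, × 0.96 | 0.0857 | 0.0574 | 1905 | 90.5% | 90.3% |
| two years, × 0.96² | 0.0823 | 0.0551 | 1984 | 89.3% | 89.2% |

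So 1936 lies inside the range obtained with no clustering term. The ratio of 1936 to the requirement is 1936/1829 = 1.06, 1936/1905 = 1.02 and 1936/1984 = 0.98. A score-type formula (Signorini) needs fewer patients, about 1605 to 1742 over the same three baselines, which leaves a factor of 1936/1742 = 1.11 to 1936/1605 = 1.21.

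**3. Reading r as an intraclass correlation.** The usual design effect for comparing whole clusters is 1 + (m − 1) × ICC. With m = 482 this is 1 + 481 × 0.3 = 145.3. None of the calculations tried with that factor comes near 1936.

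**4. Reading r as something else.** Small multipliers built from 0.3 can also land near 1936:

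- baseline 0.0893 × 0.96, RR 0.63 (33% plus 4 points), Wald: 1485 × 1.3 = 1931;
- baseline 0.0893, RR 0.67 × 0.96, rate-difference formula: 1519 × 1.3 = 1974;
- baseline 0.0893, RR 0.67 × 0.96, Signorini formula: 1336 / (1 − 0.3) = 1909.

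The article states none of these, and none depends on the number of patients per hospital.

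**5. The planned contrast.** Assume that 1936 a year covers both unit types and is split equally, 968 each, with baseline 0.0893, a common trend of 0.96 and RR 0.67 in Phase I. Expected events per cell are:

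- Phase I: 968 × 0.0893 = 86.4 before, and 86.4 × 0.96 × 0.67 = 55.6 after.
- Phase II: 86.4 before, and 86.4 × 0.96 = 83.0 after.

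The variance of the log ratio of rate ratios is 1/86.4 + 1/55.6 + 1/86.4 + 1/83.0 = 0.0532, so SE = 0.231. Then 0.4005 / 0.231 = 1.737, and power = Φ(1.737 − 1.960) = 41%. If the 33% already includes the trend, RR = 0.67 / 0.96 = 0.698 and power is 35%. Both figures come before any unit-by-period variance. If 1936 were meant for each unit type, the variance halves, the ratio becomes 1.737 × √2 = 2.456, and power is Φ(2.456 − 1.960) = 69%.

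**The case against.** The article never calls r an intraclass correlation. It could be a correlation between periods or a squared multiple correlation, and step 4 shows that modest multipliers reach 1936 about as closely as the unclustered formula does (1905 is itself 1.6% off). This stands: the close unclustered match does not prove that no adjustment was made. A reader might infer that the size cannot have accounted for clustering, but that is shown only on the intraclass reading.

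A reader might also infer that 1936 patients are worth only about 13 (1936 / 145.3), or that some 266,000 to 277,000 a year would be needed (1829 or 1905 × 145.3). The documents do not support this. The factor of 145 applies when whole hospitals are compared. Here every hospital supplies Phase I and Phase II units in both years, so a common hospital effect largely cancels. What would matter is variation between units and between periods within units, and the article gives no figure for either.

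Finally, an article may leave the full formula to a longer protocol, and the site discrepancy is trivial in size. Both are fair. The point here is not a missing formula. It is a stated power claim with an unidentified parameter, for a number that does not visibly contain the claimed allowance, and two figures in one sentence that disagree.

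**Conclusion.** The two size figures contradict each other: 1928 against 1936, a gap of 8 patients a year with about 0.1 point of power at stake. This needs no assumption beyond the four sites.

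The statement that 90% power accounts for hospital clustering is not supported as written. On the intraclass reading, r = 0.3 is incompatible with 1936 under the standard design effect. On any other reading, the sentence does not identify what was adjusted for. With two-sided 0.05 assumed and no clustering term, the Wald calculation gives about 1830 to 1980 per year, so the stated number corresponds to a simple two-period comparison with little or no room for inflation (up to about 1.2 on a score-type formula).

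The more consequential gap is that the 90% does not carry over to the planned interaction. Power there is about 40% (35% to 41%) with an assumed equal split of 968 per unit type per year, and 69% even if 1936 applied to each unit type, both before unit-by-period variance. These figures depend on the split and on how the trend enters, neither of which the article states.

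**What to change.** - Reconcile the target: change 482 to 484 per site, or 1936 to 1928 in total.
- Say what r is and show the inflation applied, or withdraw the statement that the 90% is net of hospital clustering.
- State alpha and sidedness for this outcome, how the 4% trend enters, and whether 1936 covers both unit types.
- Restate the power for the unit-type-by-period interaction with the actual split between Phase I and Phase II units. Present any allowance for unit-by-period variance as an assumption with a range.

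The cost is one corrected figure, some rewording and a short recalculation. The planned analysis and data collection are unaffected, and the study does not have to be enlarged; the interaction result would be reported with its realistic precision.

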### Qualitative data collection

We use a multi-method approach to collect and triangulate data from numerous sources at each of the study sites. Site visits form the basis of the data collection and provide the opportunity to conduct ethnographic observations, semi-structured interviews, and focus groups.

#### Observations

We conduct a series of ethnographic observations during the site visits to help us understand each hospital’s local context and how unit-specific contextual factors affect the adaptation and implementation of the intervention components [49, 50] (e.g., observe physician and nurse work activities, interprofessional rounds) (see Additional file 2). In addition, we tour the medical units to observe physical spaces and have conversations with hospital staff in their own environment. The site team assumes the role of “peripheral-member-researcher” which brings an insider’s perspective to the observations to allow accurate appraisal of activities [51].

#### Interviews

We conduct semi-structured interviews with key stakeholders at each site [52, 53] (see Additional file 3). Participants include the site leadership team (physician leader, nurse leader, and research nurse), Chief Medical Officer, and Chief Nurse Officer. Interview data is an important source of the information about how individuals think about quality, local culture, and the effectiveness of the interventions. Interview questions focus on assessing the local adaptation and implementation of each component, as well as the individual’s perceptions of the utility of each component.

#### Focus groups

We conduct focus groups in each hospital using a set of semi-structured questions to guide discussion. Focus group participants include the site leadership team, hospitalists, nurses, and the hospital professionals involved in implementation at the microsystem level (e.g., unit co-leaders). The data from the focus groups provides important information about issues related to each intervention and how site team members interact with one another.

#### Artifacts

Artifacts are “the implements, notes, or materials” used during the adaptation and implementation of the interventions (e.g., hospital application, notes from mentor calls, structured communication tools, unit performance reports) [54]. Analysis of these artifacts will provide additional information about site-specific contextual factors [55].

#### Qualitative data analysis

Each researcher takes detailed notes of observations and discussions during interviews and focus groups. Notes will be analyzed using a computer-assisted qualitative data analysis software (MAXQDA). During analysis, categorical themes will be identified and applied. We will conduct a hybrid form of analysis which will combine inductive and deductive logics [56, 57]. The analytic strategy is informed by the task at hand (evaluation of the adaptation and implementation of the interventions), as well as the desire to allow unanticipated themes to emerge from the data and to allow participants’ understandings to come to the fore [58]. Deductively, we will begin by imposing a priori categories that serve the needs of the evaluation. While the first dimension is chronologically ordered (Exploration, Preparation, Implementation, Sustainment), the second dimension adapts the conceptual framework for analyzing textual data proposed by Corbin and Strauss [59]. We will use cross-case comparisons to consider how site-specific contextual factors interact with the variation in the intensity and fidelity of implementation to affect teamwork and patient outcomes [60]. Generalizability will be increased by providing details of the changes and contextual factors of each hospital.

### Timeline

A high level timeline for the RESET study is provided in Figure 3. Exploration and Preparation occurred in year 1. Sites began to implement the AIMS interventions on Phase I units in year 2 (Implementation Phase I). Sites implement the AIMS interventions on Phase II units in year 3 (Implementation Phase II). Sustainment occurs in year 4 and program analysis occurs in year 5.

**Fig. 3 Fig3:**
[figure not shown]
RESET Study Timeline (SPIRIT diagram of trial stages of enrollment, intervention, assessment, and evaluation)

## Discussion

A number of challenges impede our ability to consistently provide high quality care to patients with medical problems. The RESET study uses a clinical microsystems framework and a set of complementary, mutually reinforcing interventions to redesign systems of care for hospitalized medical patients. Quantitative data will allow us to evaluate the effect the interventions on teamwork climate and patient outcomes, while qualitative data will allow us to assess how site-specific contextual factors influence adaptation of the interventions and influence the success of implementation.

### Strengths

The RESET study has several notable strengths. First, the majority of prior studies have evaluated the effect of single interventions to redesign aspects of care delivery for patients hospitalized with medical conditions. RESET will assess the effect of a set of complementary and mutually reinforcing interventions (i.e., the AIMS interventions). Second, RESET uses an established mentored implementation approach and interprofessional site and mentor teams. Third, our phased implementation allows lessons learned in early implementation to be incorporated into later implementation efforts, and provides for a rigorous evaluation using both historic and concurrent controls (i.e., difference-in-differences analytic strategy). Most prior studies have used a before-and-after study design which does not account for baseline trends in outcomes assessed. Fourth, we provide resources for collection of fidelity and outcome measures. Providing fidelity measures to sites on a regular basis allows them to identify areas for improvement and make adaptations. Finally, our qualitative assessment will allow us to describe how sites have adapted the interventions and contextual factors which influenced the success of implementation.

### Challenges

We anticipated several challenges with the RESET study. Even with the rigorous support provided, sites have found the redesign of hospital systems to be difficult. The biggest challenges thus far relate to unit-based physician teams, unit nurse-physician co-leadership, and enhanced interprofessional rounds. With regard to unit-based physician teams, sites have had to make fundamental changes to their processes for assigning newly admitted patients to physicians. Sites are now designating specific physicians to care for patients on specific units and newly admitted patients are assigned to a physician based on their unit location.

The implementation of unit nurse-ohysician co-leadership has been challenging because sites have struggled to provide protected time for unit physician leaders to serve in this role. Additionally, some sites have felt that they have few talented and/or interested physician leaders to serve as a unit physician leader. Mentors have coached teams in advocating for this role and selection and training of potential physician leaders.

Of note, all sites have decided to implement enhanced interprofessional rounds at the bedside. Site teams have had to address key issues when planning the implementation of enhanced interprofessional rounds, including the determination of which professionals should be present, the optimal duration, and whether interprofessional rounds should be combined with the physician’s planned encounter for the day. Regarding the latter, most sites have planned to have physicians visit patients before interprofessional rounds to discuss more detailed medical issues and perform physical examinations.

### Dissemination and impact

Findings from this study will be directly applicable to all hospitals caring for patients with general medical conditions. Importantly, the study was informed by, and leverages the expertise and influence of a diverse group of stakeholders, including SHM, the ANA, and the Institute for Patient- and Family-Centered Care. These stakeholder groups continue to provide critical input and will be instrumental in disseminating our findings.

## Abbreviations

AIMS: Advanced and Integrated MicroSystems
ANA: American Nurses Association
EPIS: Exploration, Preparation, Implementation, Sustainment
HCAHPS: Hospital Consumer Assessment of Healthcare Providers and Systems
MPSMS: Medicare Patient Safety Monitoring System
ORIC: Organizational Readiness for Implementing Change
RESET: Redesigning Systems to Improve Teamwork and Quality for Hospitalized Patients
SAQ: Safety Attitudes Questionnaire
SHM: Society of Hospital Medicine
